### Interim analyses

For stage 1 interim analysis, only the primary outcome will be formally analysed using the generalised linear model described above. We designed the trial to have a non-binding futility bound with a one-sided *p* value of 0.3. The significance level will be used as the critical value for the *p* value of the observed treatment effect as this controls the type I error rate at the nominal level regardless of the true control event rate [45].

The measures to safeguard the confidentiality of the interim analysis results and minimise potential operational bias are detailed below:The independent DMC will receive a closed report prepared by the unblinded trial statistician showing the between-group differences of each intervention arm compared with TAU.If both intervention arms meet the criteria to continue in stage 2 (one-sided *p* value ≤ 0.3), no interim analysis results will be shared with the TMG or TSC, and the study will continue as three-arm trial, provided this is endorsed by the TSC on the recommendation of the DMC.If one or both interventions arms just exceeds the threshold for futility (one-sided *p* value > 0.3 and < 0.4), we will provide the DMC with additional information about the between-group differences on the CSSRS to guide a decision on whether one or both arms should continue in stage 2.If one intervention arm clearly exceeds the threshold for futility (one-sided *p* value ≥ 0.4), or if following the additional information on CSSRS the DMC recommends dropping one arm, the interim analysis results for this comparison only will be shared with the TMG and TSC on the recommendation of the DMC. This arm will be dropped from stage 2 of the study. The interim analysis results of the remaining arm will not be shared with the TMG or TSC.If both arms are recommended to be dropped, following confirmation of the recommendation of the TSC by the funder and sponsor, we will terminate recruitment to the study for lack-of-benefit in either arm.

### Methods for additional analyses (e.g. subgroup analyses)

There is no pre-specified subgroup analysis.

### Methods in analysis to handle protocol non-adherence and any statistical methods to handle missing data

All analyses, both interim and final analyses, will be conducted on the intention-to-treat (ITT) sample (i.e. all randomised will be analysed according to which study arm they have been allocated, regardless of the intervention or treatments actually received, adherence to treatment, or the number of measurements recorded).

The per-protocol population (PPP) will be defined as all participants that adhered to the interventions’ protocols, and participants that are classified as non-adherers will be removed from the PPP sample. Adherence is defined as follows for the treatment arms:SAFETEL: attending the initial safety planning session and at least one follow-up callPREVAIL: attending at least two peer support sessions

Analyses for the primary outcome (hospital admissions) will be repeated on the PPP sample as supplementary analyses at stage 2 only. If the proportion of adherence for any of the interventions is found to be lower than 80%, a complier average causal effect (CACE) analysis will be considered to investigate the effect of actually receiving the intervention on the primary outcome.

Maximum likelihood estimation provides valid inferences under the assumption that the missing data mechanism is ignorable (or missing at random). We anticipate low levels of attrition for the primary outcome (< 5%). We will check for baseline predictors of missingness in the secondary outcomes at 6 months and if identified include these in the analysis model as a sensitivity analysis.

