#### PREVAIL

PREVAIL is a brief, psychosocial intervention delivered by Peer Support Workers (PSWs) employed by the NHS and is delivered by telephone or videoconference [25]. Participants allocated to the PREVAIL intervention are offered up to 12 sessions of the intervention over a 3-month intervention period. The key components of the PREVAIL intervention include common elements of peer support (PS) such as supportive listening and PSW sharing recovery stories, improving hope and belongingness, managing acute suicide risk including safety planning, maintaining both peer and PSW wellness and principles of motivational interviewing. PREVAIL is delivered in three phases: (i) assessment and getting to know you, (ii) active involvement and (iii) ending and consolidation.

Semi-structured conversations incorporate suicide prevention strategies derived from CBT and motivational interviewing (MI), including goal setting, distress tolerance, and increasing optimism and social connectedness. These conversations use a standardised format including the steps of Invite, Learn, Share and Motivate. In the Invite step, permission is sought from the participant to have a conversation about a hope or belongingness-related topic. During the Learn step, information regarding what the participant has already tried and what the participant thinks might be helpful or relevant to their situation is elicited. During the Share step, helpful suggestions are made based on the PSW’s personal experience or knowledge. The Motivate step engages the participant in ‘change talk’, including how acting might be helpful to them and how they might implement changes.

The final phase, focusing on endings, consolidation and future directions (including future access to peer support), will span sessions 11–12 (approximately), although endings and the time-limited nature of PREVAIL will be regularly discussed throughout all phases. The PSW may transition to a step-down phase at session 10 by moving to fortnightly contact. The aim of the final sessions is to consolidate learning, review what has been helpful and develop a plan to maintain gains. The format of delivery will be flexible throughout the 12 sessions.

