#### BrighterSide smartphone app

BrighterSide is a self-guided smartphone app to help those with suicidal thinking to understand their thoughts and develop the best skills and strategies to help manage them [24]. The app contains five modules that are primarily based on CBT and DBT. The module topics are (1) Understand Your Thoughts; (2) Prevent a Crisis; (3) Navigate your Emotions; (4) Navigate Your Thoughts; and (5) Plan for the Future. BrighterSide allows users to personalise their experience with the following key features: develop a personalised safety plan, daily check-ins to help users connect with their feelings (this option can be skipped), coping tools including claiming and distracting techniques, pathway selection through the app based on the user’s preference and favourites to allow users to save their favourite activities and content. Content is not time-gated, with all five modules available immediately on installation and can choose which pathway or activities they wish to complete.

All participants allocated to BrighterSide are provided by the study team with a smartphone with the BrighterSide app installed and the app is activated by the participant with an access code provided by the study team as part of onboarding. Onboarding and offboarding is by a study AP or other non-blind member of the trial team. Access to BrighterSide app is exclusively for use in a clinical trial and access is removed on exit from the study. Participants can email themselves a copy of their safety plan from within the app at any time and at offboarding. BrighterSide collects usage data that facilitates monitoring of fidelity and adherence with the intervention. Adherence is defined as engagement with at least two of the five modules.

There are no criteria for discontinuing or modifying allocated interventions.

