### Outcomes

#### Primary outcome

The primary outcome is any admission to a psychiatric hospital admission over 6 months (treated as a dichotomous yes/no variable) which is obtained by screening the participants’ electronic patient records (EPR).

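### The one firmly planned adherence analysis drops non-adherers from SAFETEL and PREVAIL only, so early admissions can leave the active arms with their events and create an apparent benefit; CACE should be the committed analysis

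*Protocol article*

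**What the plan says.** All of the rules are in the Protocol article, section on protocol non-adherence and missing data. Interim and final analyses "will be conducted on the intention-to-treat (ITT) sample". A per-protocol population is then formed, from which "participants that are classified as non-adherers will be removed from the PPP sample".

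The criterion is introduced with "Adherence is defined as follows for the treatment arms", and two definitions follow. SAFETEL needs the first safety-planning session plus one further call. PREVAIL needs two sessions. TAU has no criterion.

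The commitment is firm: "Analyses for the primary outcome (hospital admissions) will be repeated on the PPP sample as supplementary analyses at stage 2 only". The alternative is conditional: if adherence to any intervention falls below 80%, "a complier average causal effect (CACE) analysis will be considered".

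Two other sections fix the timing. Under Primary outcome: "The primary outcome is any admission to a psychiatric hospital admission over 6 months". Under PREVAIL, participants "are offered up to 12 sessions of the intervention over a 3-month intervention period", and the SAFETEL section offers the same number of sessions over the same period. Adherence is thus achieved, or not, within the first half of the window in which admissions are counted.

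**The concern.** The removal rule acts on one side of each comparison. Someone on SAFETEL or PREVAIL who is admitted before a second contact may be classed as a non-adherer and leave the analysis with the admission. Someone on TAU who is admitted on the same day stays in and counts as an event. The section says nothing about participants admitted before they could meet the definition.

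This goes beyond the usual caution about per-protocol analyses, because the event that can block adherence is the primary outcome itself. Early admissions are also plausible. The Eligibility criteria recruit people in crisis care now or within the previous 14 days, on the ground that this marks a raised near-term risk of admission.

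At stake is the reading of a supplementary result. If the intention-to-treat result is borderline, a more favourable per-protocol result could be taken as support, although part of it may come from the removal rule.

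**Working it through.** **Reproducing the design.** The Sample size section gives 15% admission on TAU, a 7.5-point difference, one-sided alpha 0.025, 90% power and 5% loss. Allocation is 2:2:3. With unpooled variance:

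n(TAU) = [0.15×0.85 + 0.075×0.925×1.5] × ((1.960+1.282)/0.075)² ≈ 432.6, so 433 TAU and 289 per active arm.

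The total is 433 + 2×289 = 1011, and 1011/0.95 = 1064.2, against 1064 stated. The analysed sizes used below are therefore 433 against 289.

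**Bias with no treatment effect.** Let p = 0.15 in every arm. Let f be the share of 6-month admissions that occur early enough to prevent adherence. The documents do not give f, so it is an assumption shown over a range. Removing those people from an active arm gives:

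- adherence = 1 − pf
- admission risk in those kept = p(1−f)/(1−pf)
- false benefit = p − that risk

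The last column is the normal-approximation chance of one-sided p<0.025, with n = 433 on TAU and 289(1−pf) in the active arm.

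| f | adherence | risk kept | false benefit | p<0.025 |
|---|---|---|---|---|
| 5% | 99.2% | 0.1425/0.9925 = 14.4% | 0.6 points | about 4% |
| 10% | 98.5% | 0.1350/0.985 = 13.7% | 1.3 points | about 7% |
| 20% | 97.0% | 0.1200/0.970 = 12.4% | 2.6 points | about 16% |

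At f = 20% the false benefit is 2.6/7.5 = 35% of the target difference.

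Simulation at 433 against 289 agreed for f = 10% (1.3 points, 6.6%) and f = 20% (2.6 points, 16.1%). In the same simulations intention-to-treat was centred on zero and rejected in 2.4%.

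**A reference value for f.** If admissions were spread evenly over 26 weeks and two weekly contacts took 2 weeks, f = 2/26 = 7.7%. The risk in those kept would be 0.1385/0.9885 = 14.0%, a false benefit of about 1.0 point. Front-loaded admissions would raise f. Contacts completed during or after an admission would lower it.

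**The 80% trigger.** From this mechanism alone adherence stays at 97% to 99% over the range, and at 92.5% even if f were 50%. The condition for considering CACE would not be met. Adding 10% to 20% non-adherence unrelated to risk leaves the false benefit unchanged. It can take adherence below 80%, but CACE is then still only to be considered.

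**Direction when non-adherence has other causes.** With 20% non-adherence and overall risk 15%, the risk in adherers is (0.15 − 0.2r)/0.8, where r is the risk in non-adherers:

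- r = 30%: 11.25%, or 3.75 points for the intervention
- r = 15%: 15%, no bias
- r = 5%: 17.5%, or 2.5 points against the intervention

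**The case against.** The strongest reply is that inference is protected. Intention-to-treat governs the interim and final analyses. The per-protocol run is labelled supplementary, is confined to stage 2, and drives no arm selection, sample size or alpha. That stands. A reader might infer that the trial's main conclusion is compromised; it is not.

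The second reply is that the mechanism is limited here. The threshold is two contacts out of up to 12, delivery is by telephone or videoconference, and, in a sentence placed under BrighterSide but worded generally, "There are no criteria for discontinuing or modifying allocated interventions". Nothing says that an admission ends the sessions, so some people admitted early could still meet the definition and stay in with their event. This also stands, and it is why the range runs from small values of f.

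Third, a reader might infer that the analysis must favour the interventions, or must do so by a large amount. The documents do not support either. The sign reverses if non-adherers are mainly people who recovered quickly. The 3.75-point case needs 0.2×0.30/0.15 = 40% of active-arm admissions to fall among non-adherers, for which the protocol gives no basis. Larger values obtained by assuming 70% adherence lie below 80%, where CACE already comes into consideration.

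Fourth, if TAU participants cannot receive the interventions, CACE at 80% adherence or more is at most 1/0.8 = 1.25 times the intention-to-treat difference and tests essentially the same null, so a trigger can be defended. That is fair as a comment on how much CACE adds. It does not justify making the biased contrast certain and the randomisation-based one optional. Nor is this detail properly left to the analysis plan: the protocol itself states the removal rule and the condition for CACE.

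**Conclusion.** The point holds in a bounded form. The protocol commits to an adherence analysis that can remove events from the active arms but not from TAU, and leaves optional the method that respects randomisation. With no true effect and f between 5% and 20%, the early-admission mechanism produces a false benefit of about 0.6 to 2.6 points, with one-sided p<0.025 in about 4% to 16% of trials against a nominal 2.5%.

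This rests on 15% risk in all arms, on analysed sizes of 433 and 289, and on an assumed f. The direction is firm for this mechanism and not for non-adherence as a whole. Because the per-protocol output cannot show which kind of non-adherence dominates, neither the sign nor the size of its bias can be read from it. The matter should be corrected, but it does not threaten the primary analysis or the sample size.

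**What to change.** Commit to a CACE analysis of the primary outcome at stage 2 for each intervention against TAU. Use randomised allocation as the instrument and the adherence definitions already stated, and run it whatever the observed adherence. Name it as the planned adherence analysis. Under no effect it is centred on zero, as intention-to-treat is.

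The per-protocol analysis need not be deleted. If it is kept, label it descriptive, not a causal estimate and not evidence of efficacy.

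The cost is a wording change and one extra model per arm. Intervals will be wider than those of the naive per-protocol estimate. CACE also relies on the exclusion restriction: allocation has no effect in those who do not meet the adherence definition. That needs comment for SAFETEL, whose section places the core component, the safety plan, in the first session. A participant who attends only that session counts as non-adherent but has received it.

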### Plans to give access to the full protocol, participant-level data and statistical code

These will be managed and held by the King’s CTU. Requests for access to the dataset and analysis code will be considered in the first instance by the Chief Investigator and then the King’s CTU.

## Health economics and cost-effectiveness methods

A within trial economic analysis will compare the net costs and health benefits of the included interventions (PREVAIL and SAFETEL) plus TAU to TAU alone over the 6-month trial follow-up, from the NHS and social care (costs) and patient (health benefits) perspective. The primary measure of health benefit will be quality-adjusted life-years (QALYs) estimated from the EQ-5D-5L and the utility tariffs recommended by NICE at the time of the analysis. Health and social care service use (self-report supplemented by electronic medical record review for psychiatric hospital admission data) and EQ-5D-5L data will be collected for each participant at baseline, 3 months and 6 months. Self-reported service use data will be collected using an Economic Patient Questionnaire (EPQ) developed and used by the applicants in previous trials in severe mental illness and adapted for this study. The UK literature recognises that issues with electronic routine data sources may result in self-reported data being the preferred option [46]. Due to the unfeasible nature of accessing and extracting full-service use from routine electronic data sources, the trial will collect psychiatric inpatient admissions from hospital record data (these are likely a key driver of costs in this population). With the rest being taken from the self-report questionnaire (EPQ), collected during interview. Items of resource use will be multiplied by published national health and social care costs (Department of Health Reference Costs; Unit Costs of Health and Social Care, PSSRU). The EPQ will be discussed and piloted with the SURG prior to being finalised for the start of the trial.

Multiple imputation will be used to impute missing observations. The analyses will control for key baseline covariates or characteristics (demographic, socio-economic and clinical measures) identified from the published literature and supplemented with analysis of pooled baseline data. The cost and outcome effects will be bootstrapped to generate incremental cost-effectiveness ratios, cost-effectiveness acceptability curves and net benefit statistics. Cost-effectiveness acceptability curves (CEACs) will be plotted to summarise uncertainty associated with the ICER. To derive CEACs, the incremental cost and QALY (effect) estimates from the regression analyses will be bootstrapped to simulate the sample data of costs and QALY. The bootstrapped estimates of net QALYs will be revalued, using a range of ceiling ratios or willingness to pay thresholds (WTPT) to gain 1 QALY.

In the UK, there is no universally agreed cost-effectiveness threshold value. One commonly reported threshold is from NICE in England of approximately £20,000 to £30,000 per QALY [37]. However, there is a lack of consensus around the appropriate threshold [47, 48]. Therefore, the monetary value of simulated QALYs will be varied from £0 to £30,000 to reflect a range of hypothetical willingness to pay thresholds. As the analysis is comparing multiple options, a sensitivity analysis will adopt a fully incremental approach. Sensitivity analyses will also assess the choice of health benefit measure (QALYs calculated using ReQOL-10 as an alternative measure) and the impact of missing data (complete case versus imputed data). All economic analyses will be pre-specified in a Health Economic Analysis Plan (HEAP) to be agreed with the TSC and DMC. Reporting will be in line with the Consolidated Health Economic Evaluation Reporting Standards 2022 (CHEERS 2022) statement [49].

## Oversight and monitoring

### Composition of the coordinating centre and trial steering committee

The University of Manchester is the primary sponsor for the study. The day-to-day running and organisation of the RAPID trial is coordinated by a central management team comprised of the Chief Investigator (CI), a Trial Manager and a Clinical Trial Manager, and the site management teams that are comprised of a Principal Investigator (PI), site leads/coordinators and local clinical supervisors (where this function is not provided by the PI). The central management team meets on a weekly basis, and an extended meeting each month to ensure oversight of the study and coordinates a monthly Trial Management Group (TMG) meeting attended by the central management, site management teams, co-investigators and the sponsor. The site management teams meet with the RAs and interventionists for a weekly team meeting to ensure there is regular communication and interaction between site leads, local clinicians and research staff. One member of the central management team attends the site team meetings at a minimum of once per month to ensure central management presence and support. Each staff group receives the following: (1) local clinical supervision for personal wellbeing, risk management, problem solving local issues and compliance with local NHS policy; (2) a weekly/bi-weekly central management supervision to ensure compliance to the study protocol, reliability in conducting research assessments or fidelity to the intervention manual; and (3) a weekly/bi-weekly group supervision with their peers (chaired by a member of the central management team) to ensure across site peer connection/support, learning and consistency.

Independent oversight of the trial is provided by an independent DMC and a TSC. Full details of the DMC are provided below. The TSC is comprised of an independent chairperson, a statistician with expertise in MAMS design and analysis, two clinicians with expertise in SMHP and inpatient settings, and a service user along with non-independent members; the CI, trial manager, a representative of the funder and a representative of the sponsor are invited to attend. The TSC meet every 6 months and the meetings occur around 2 weeks after the DMC to ensure all the DMC recommendations are considered by the TSC. The funder is provided with the minutes of the DMC and TSC meetings along with a summary of the committee’s recommendations and actions taken. Both the DMC and TSC approved the study protocol ahead of the study commencing recruitment and review the internal pilot data against the a priori progression criteria with recommendations for the funder. The DMC and TSC shall review the interim analysis data; however, only the DMC shall have sight of unblinded data.

### Composition of the data monitoring committee, its role and reporting structure

The composition of the DMC is an independent chairperson, a statistician with expertise in MAMS design and analysis, and a clinician with expertise in serious mental health problems and inpatient settings. To facilitate the meeting, the CI, Trial Manager and study statisticians attend the DMC to facilitate the meeting and the sponsor invited to attend. The DMC meets six monthly, but major trial issues can deal with between meetings, by phone or by email. An open and closed format is used for the meeting and only independent members of the DMC and the unblinded trial statistician have access to unblinded data. For the open sessions, the meeting focusses on recruitment, retention, data quality (e.g. data return rates, treatment compliance) and adverse/serious adverse events. The closed session focuses on safety data by treatment group and selected secondary outcomes the randomised groups are labelled A and B, with the identity of A and B provided by the study statistician separately to the report. A copy of the DMC charter is retained by the trial manager in the site file.

